#### Take-Home Assessments

##### Psychological Health

For the psychosocial outcomes, health-related quality of life is measured with the short version of the *World Health Organization Quality of Life* assessment [91-94]. This includes 24 questions organized around four domains: physical health (seven items), psychological health (six items), social relationships (three items), and environment (eight items). There are two additional questions on overall health-related quality of life and general health. Each question is rated on a 5-point Likert interval scale ranging from 1 (poor) to 5 (good). At the end, scores for each question and a mean score computed for each domain are reported. To further investigate psychosocial outcomes, the *Beck Depression Inventory* [95], the *Beck Anxiety Inventory* [96], and the *Psychological General Well-Being Index* are used [97-99]. The *Beck Depression Inventory* and the *Beck Anxiety Inventory* are each comprised of 21 groups of statements that are evaluated on 4-point Likert scales, with higher scores indicating higher depressive or anxiety-related symptoms, respectively. The *Psychological General Well-Being Index* includes 22 items organized around components of psychological well-being, such as anxiety, positive well-being, self-control, depression, and general health and vitality. Response options for each item are individualized according to the given affective experience. Intensity or frequency of experience during the past month is rated on a 6-point Likert scale ranging from 0 (most negative option) to 5 (most positive option).

##### Participant Satisfaction and Perspectives

For participant satisfaction, an updated version of the *Montreal Walking Exoskeleton Satisfaction and Perspectives Questionnaire* (MWESP-Q) is completed online at T_2_. This questionnaire includes 54 statements that are organized around seven key domains: overall satisfaction related to the training program (two statements); satisfaction related to the overground robotic exoskeleton (seven statements); perceived learnability (12 statements); satisfaction related to the program attributes (eight statements); perceived health benefits (12 statements), including sentences that relate to pain, spasticity, bowel functions, and sleep; perceived risks and fears (11 statements); and perceived motivation to engage in regular physical activity (two statements). Each statement is rated using a 7-point Likert scale ranging from 1 (most negative option; eg, strongly disagree) to 7 (most positive option; eg, strongly agree) [64].

For participants’ perspectives, a 20-30-minute semistructured interview is conducted over the phone to capture their general experience when participating in the wearable robotic exoskeleton–assisted training program. The interviews also serve as a platform for documenting participants’ perspectives on the future of wearable robotic exoskeleton technology. To do so, various themes are discussed: potential benefits and recommendations for wearable robotic exoskeleton–assisted walking during the acute and subacute phases following spinal cord injury (eg, timing and conditions) or in a clinical setting during the chronic phase; opportunities for improvement (eg, functionality and structural aspects of the wearable robotic exoskeleton); and recommendations for a future home- or community-based wearable robotic exoskeleton–assisted walking program (eg, stairs, different surfaces, donning and doffing the wearable robotic exoskeleton without assistance, and operating the wearable robotic exoskeleton without assistance). The research professional who conducts these interviews has never met the participants and is not a member of the research team. All interviews are recorded to later enable verbatim transcription.

### Statistics

#### Sample Size Estimation

The sample size estimate was based on a comparison using the variability of the absolute change (ie, mean ±SD) in both body composition and bone mineral density (ie, main outcomes) measured pre- and postintervention in our preliminary study [61] and computed with a computerized sample size calculator [100]. Considering the self-controlled design of the study, a total of 18 participants are required to have an 80% chance of detecting a significant increase at the 5% level in the leg lean body mass (kg) at the tibia measured by DXA from 14.0 to 15.8 ±2 mg/cm^3^ [61]. Likewise, a total of 18 participants are required to have an 80% chance of detecting a significant increase at the 5% level in the bone mineral density (mg/cm^3^) at the tibia measured by pQCT from 466 to 532 ±70 mg/cm^3^ [61]. Considering the dropout rate of 7.1% found during the feasibility study [46], an additional 2 participants were added for a total sample size of 20 participants.

#### Quantitative and Qualitative Analyses

Descriptive statistics (eg, mean, SD, and 95% confidence interval) will be calculated for data summarizing sociodemographic characteristics as well as clinical and laboratory outcomes collected at the different measurement times. The normality of all data distributions and the absence of outliers will be verified via the Shapiro-Wilk test of normality and the absence of studentized residuals greater than ±3 SDs, respectively. Whenever applicable, the level of significance will be set at *P*≤.05 for all statistical tests and the data will be analyzed using SPSS, version 25.0 (IBM Corp).

For Hypothesis 1, one-way analysis of variance for repeated measures (ie, normally distributed continuous data) or Freidman tests (ie, non-normally distributed continuous or categorical data) with planned comparisons based on the hypothesis and Bonferroni correction will be conducted to detect significant time effects, with a special interest for the preintervention (T_0_ vs T_1_), intervention (T_1_ vs T_2_), and retention (T_2_ vs T_3_) phases. In accordance with the principles of a classic intention-to-treat approach, all participants will be included in the final analyses, regardless of withdrawal, compliance, or unintentional missing data. For missing data, imputation of the mean value for the specific group at the specific assessment time will be used. Per-protocol exploratory analyses will also be performed comparing outcomes for those with walking program compliances of greater than 75% to examine maximum treatment efficacy.

For Hypotheses 2 and 3, Pearson or Spearman correlation coefficients will investigate the strength and direction of the relationships between the overall observed changes ([T_1_–T_2_] / T_1_ × 100) for each personal factor (ie, dependent variable) and the program characteristics (ie, independent variable). Independent variables having reached a critical threshold (*P*≤.25) will then be confronted in a stepwise multiple linear regression analysis to identify the three best predictors for each dependent variable and the coefficient of determination (*R^2^*) of the model. To determine the factors for identifying the best responders to the program, analyses similar to the previous ones will be completed, except that the independent variables will be sociodemographic characteristics, anthropometric parameters, characteristics of the SCI, personal factors, and functional disability.

For Hypothesis 4*,* using Microsoft Excel, descriptive statistics of the 54 statements (ie, mean, median, and SD) will summarize the results of the satisfaction survey (ie, the MWESP-Q). Audio recordings of the interviews will be transcribed verbatim using Microsoft Word. A summer research intern will read the transcripts and generate initial codes or subthemes. A co-codification of the first transcript will be done manually on printed paper with the list of initial codes and subthemes; this will be done independently by three research collaborators (ie, a summer research intern, a doctoral student, and a researcher who is a member of the research team). They will write codes directly in the margin of the printed transcripts. They will then meet via audio and video conferencing to compare and review coding, discuss discrepancies, and modify codes if necessary. This process will be done twice with the transcripts of the first two participants. To start the computerized qualitative analysis, all transcripts will be interpreted using thematic content analysis, where narrative data will be thematically coded and appraised using NVivo 10 (QSR International). A final report, integrating findings from the MWESP-Q and the interviews, will be produced and recommendations will be incorporated in order to shape the development of a future home- or community-based adapted physical activity program.

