## Methods

### Study Design

A prospective, longitudinal, self-controlled interventional study with multiple discrete measurement times will be used to assess outcomes at baseline (ie, preintervention phase), during the intervention, and thereafter (ie, retention phases) (see Figure 2). While this design may contrast with *classic* study designs frequently recommending a separate comparison group to assess efficacy or effectiveness, the use of a separate comparison group was judged as nonideal in the context of this study, based on the challenges linked to the classification and quantification of the severity of SCIs and their heterogeneous consequences [65]. In addition, interventional trials of new technologies document that potential participants are reluctant to participate, refuse to adhere to the requirements of a control group, or withdraw for the most part from a control group [66,67]. To strike an optimal balance between the need to have a control group with the anticipated strong desire of potential participants to engage in the wearable robotic exoskeleton–assisted walking program, while also considering the amount of, and timeline limits linked to, the study’s funding, the study includes a 4-week observation phase prior to the start of the intervention. Since only individuals with a chronic SCI with *stable* overall health status and life habits will be recruited, outcome measures will be assessed at the start and at the end of the 4-week observation phase. These outcome measures will provide data about each participant’s natural variability and will enable us to detect whether the intervention has an effect greater than the underlying natural variability (ie, patient-specific minimal detectable change criteria computed); they will also enable us to test the effects of the intervention (ie, pre- vs postintervention responses). This boosts the ethical acceptability of the project, minimizes the impacts of potential and unmeasured confounding variables, facilitates recruitment, and mitigates the risk of experimental attrition. Lastly, semistructured interviews and an online questionnaire will capture participants’ satisfaction levels and perspectives about the wearable robotic exoskeleton–assisted walking program and the mobility technology in itself (ie, the wearable robotic exoskeleton).

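### Normality of the outcome values, rather than of within-person changes or residuals, decides between repeated-measures ANOVA and Friedman, so skew between people can send an outcome to a rank test needlessly

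*Protocol article*

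**What the plan says.** All of the relevant analysis text is in the Protocol article, Quantitative and Qualitative Analyses.

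- Normality check: "The normality of all data distributions and the absence of outliers will be verified via the Shapiro-Wilk test of normality". The sentence goes on to "the absence of studentized residuals greater than ±3 SDs, respectively". With that last word, residuals belong to the outlier check and Shapiro-Wilk to the data distributions.
- Choice of test for Hypothesis 1: "one-way analysis of variance for repeated measures (ie, normally distributed continuous data) or Freidman tests (ie, non-normally distributed continuous or categorical data".
- Follow-up: "with planned comparisons based on the hypothesis and Bonferroni correction will be conducted to detect significant time effects", with special interest in T0 vs T1, T1 vs T2 and T2 vs T3. The follow-up test after Friedman is not named.
- Level: "the level of significance will be set at *P*≤.05 for all statistical tests".

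Under Sample Size Estimation, 18 participants are said to "have an 80% chance of detecting a significant increase" at the 5% level in each of two main outcomes, leg lean mass and tibial bone mineral density. The SD is described as that of the absolute pre-post change. Two participants are added for dropout, giving 20.

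**The concern.** The design is self-controlled and each planned contrast compares a person with himself or herself. A person's general level cancels from such a contrast, so the shape of the distribution of levels across people has no bearing on whether a mean-change analysis is valid. The quantity to examine is the within-person change or the model residual. The section names neither for the normality check.

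Levels may well be skewed. The sample mixes complete and incomplete injuries, and Study Design itself cites "challenges linked to the classification and quantification of the severity of SCIs and their heterogeneous consequences". An outcome with skewed levels and well-behaved changes would then go to Friedman, which ranks each person's four visits and discards the size of the change.

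Two things are at stake. One is some power on the contrast of main interest. The other is that the inferential method for a main outcome, in a study sized on a mean change, depends on a pre-test that examines the wrong quantity.

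**Working it through.** **1. The plan's own figure.** Inputs from Sample Size Estimation: leg lean mass 14.0 to 15.8, SD 2; tibial density 466 to 532, SD 70. Standardised effects: 1.8/2 = 0.90 and 66/70 = 0.94. The independent-groups formula, n = 2(1.96 + 0.842)²/d², gives 17.7, so 18, for density and 19.4, so 20, for lean mass. Dropout: 18/(1 − 0.071) = 19.4, so 20. The stated 18 is thus reproduced for density and is within two participants for lean mass. If the SD is that of the change, as worded, a paired t test with n = 18 at two-sided 5% has 95% to 96% power. At .05/3 it has 86% (lean mass) and 90% (density). None of these figures refers to Friedman.

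**2. Efficiency of Friedman.** With normal errors and k = 4 visits, the asymptotic efficiency against ANOVA is (3/π) × k/(k + 1) = 0.955 × 0.8 = 0.764.

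**3. Simulation set-up.** From the document: four visits, n = 20 (and n = 18), effect 0.9 SD of change, three contrasts with Bonferroni (.05/3, two-sided). Assumed, because the document gives no figures: exactly normal within-person errors; effect present at T2 and T3; between-person SD three times the SD of change; lognormal skew between people with sigma 0.3 to 1; a switch to Friedman if Shapiro-Wilk rejects at any of the four visits. The mean-rank follow-up uses z = (difference in mean ranks)/√(k(k + 1)/(6n)).

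**4. How often the switch occurs although the changes are normal.**

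| Quantity tested (n = 20) | Shapiro-Wilk rejects |
|---|---|
| Visit values, sigma 0.3 to 1 | about 36% to 89% |
| Visit values, sigma 0.6 | about 73% |
| Visit values, sigma 0.6, between-person SD equal to SD of change | 53% |
| Visit values, no skew | about 12% |
| T1-T2 changes | about 5% |

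**5. Power for T1-T2 at 0.9 SD, sigma 0.3 to 1.**

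| | n = 20 | n = 18 |
|---|---|---|
| Paired t throughout | 90% to 91% | 85% to 87% |
| Plan's rule, Wilcoxon follow-up | 89% to 90% | 84% to 86% |
| Plan's rule, mean-rank follow-up | 83% to 87% | 76% to 83% |

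**6. Omnibus time effect, n = 18, sigma 1, ANOVA throughout against the plan's rule.** 0.60 SD: 83% vs 73%. 0.75 SD: 97% vs 91%. 0.90 SD: 99.6% vs 97.8%.

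**7. Type I error.** With no effect, n = 18 and normal errors, the plan's rule rejects the omnibus hypothesis in 4.6% to 4.9% of trials and T1-T2 in 1.5% to 1.9%, against a nominal 1.67%.

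**8. Where the switch helps (n = 18, 0.75 SD, omnibus).** Multiplicative outcome: ANOVA 78%, Friedman 90%. Heavy-tailed errors (t with 3 df): 95% vs 99%.

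**The case against.** The strongest reply is that little is lost. The plan names three comparisons, so a six-pair correction is not what it describes. With Wilcoxon as the follow-up, which the present wording allows, the loss is 1 to 2 points. The omnibus loss at the planned effect is about 2 points. The simulation assumes normal within-person errors, the case most favourable to ANOVA. The skew is assumed: the remark about heterogeneity in Study Design justifies the absence of a separate control group and says nothing about outcome distributions. A between-person SD three times the SD of change means 6 around 14.0 for lean mass and 210 around 466 for density, a coefficient of variation near 45%, and eligibility limits on body mass and height may make the sample more uniform than that. All of this stands, and it limits the size of the point. It does not make the values at each visit the right quantity to test.

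Three stronger readings should be resisted.

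- A reader might infer that the stated 80% power is lost. The document gives no power for Friedman, and in this scenario the plan's rule stays above 80% with n = 20. It falls below only at n = 18, with marked skew and a mean-rank follow-up that the plan does not name.
- A reader might infer that a Friedman result leaves no mean change to report. The same section promises means, SDs and 95% confidence intervals at each visit, from which mean changes follow. What is not promised is an interval for the change.
- A reader might infer that the choice of test is arbitrary. The rule and both candidate tests are stated beforehand, although the visit-level criterion is not. The word raw is also not written; it is the natural reading of the sentence.

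**Conclusion.** The point holds as a modest, inexpensive improvement. The document states a rule, so this is not a detail left to another document, and the rule examines the wrong quantity for within-person contrasts. Skew between people alone can move an outcome with normal changes to a rank test, in about 36% to 89% of simulated trials under the assumed skew, SD ratio and any-visit rule. The cost on T1-T2 at the planned 0.9 SD with n = 20 is about 4 to 8 points of power with a mean-rank follow-up and about 1 to 2 points with Wilcoxon. It is a possible cost, not a general one, because Friedman can do better when within-person errors are multiplicative or heavy-tailed. Type I error is not inflated, and no stated figure is contradicted.

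**What to change.** - **Leg lean mass and tibial bone mineral density:** name the paired mean-change analysis in advance, and report the mean change with its confidence interval.
- **Other continuous outcomes:** apply the normality check to within-person changes or model residuals. Where these are clearly non-normal, analyse on a log scale or use Wilcoxon signed-rank tests on the three planned contrasts with Bonferroni.
- **Ordinal outcomes:** Friedman can stay.

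The cost is wording only; no data collection changes and the methods are available in the named software. The downside is a slight reliance on approximate normality of the mean change at n of about 20, which a Wilcoxon sensitivity analysis for the two main outcomes would cover.

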Question 1: Does a 16-week walking program with the wearable robotic exoskeleton induce beneficial changes on musculoskeletal, cardiorespiratory, and endocrine-metabolic health; wheelchair-related functional skills and mobility; and psychosocial outcomes? Hypothesis 1: It is hypothesized that beneficial effects observed during the postintervention and retention measurement times will significantly and meaningfully exceed any changes observed during the control and preintervention measurement times (ie, T_0_ [control measurement time] vs T_1_ [preintervention measurement time] vs T_2_ [postintervention measurement time] vs T_3_ [retention measurement time]).Question 2: What personal factors best determine and predict the beneficial effects of the walking program with the wearable robotic exoskeleton? Hypothesis 2: It is hypothesized that the individuals with the highest level of SCI and the longest time since the SCI (ie, possibly the best determinants and predictors) will be those who respond best to the walking program.Question 3: What program attributes best determine and predict the beneficial effects of the walking program with the wearable robotic exoskeleton? Hypothesis 3: It is hypothesized that the total number of steps taken will be the best determinant and predictor of the measured changes.Question 4: What are the participants’ satisfaction levels with the walking program and the wearable robotic exoskeleton itself, and what are the expectations regarding its future use in the context of a home- or community-based adapted physical activity program? Hypothesis 4: It is hypothesized that WU_SCI_ will (1) express high levels of satisfaction with the walking program using the wearable robotic exoskeleton and with the wearable robotic exoskeleton itself and (2) report on how they envision its future in the context of home- or community-based use to shape the development of an adapted physical activity program in the future.

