### Outcomes: Domains, Tools, Measures, and Assessment Times

#### Overview

All outcomes reflecting the potential impacts of the intervention based on the logic model (see Figure 4) are prospectively collected at T_0_, T_1_, T_2_, and T_3_, except the participants’ satisfaction levels and perspectives and the endpoint interviews, which are only completed at T_2_. Outcomes are collected by a registered physiotherapist (AB) who has been trained with standardized data collection protocols adapted for WU_SCI_. All selected outcomes are commonly used in clinical trials targeting similar domains and populations—most have been used in the feasibility study—and most are summarized, including psychometric properties, and are recommended by well-established medical, rehabilitation, or psychosocial research organizations and networks [73]. A summary of all outcomes included in this study and the times at which they are administered is provided in Table 1. The following subsections describe all outcomes in detail.

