#### Laboratory Assessments

##### Bone Mineral Density and Architecture

A DXA system (Lunar Prodigy, GE Healthcare) is used to calculate aBMD at the hip, femoral neck, and the first to the fourth lumbar vertebrae [85]. Moreover, T-scores compare the measured aBMD values of each participant against values predicted from a matched reference group for sex, age, and ethnicity and are expressed as the number of SDs (ie, z scores or T-scores depending on age of participant). Measurements of aBMD and z scores or T-scores are directly provided by the system's software.

In addition, a peripheral quantitative computed tomography (pQCT) system (XCT 3000, Stratec Biomedical Systems) is used to characterize the volumetric bone mineral density (vBMD) and the microarchitecture parameters of trabecular and cortical bones at various imaging sites: 66% of the tibia, 25% of the femur, and 66% of the radius. These sites were chosen to maximize muscle circumference in each scan [86]. To minimize site-selection error between measurement times, images are taken using a standardized protocol including scout views with recommended reference lines [86]. As per current recommendations, reported pQCT outcomes will minimally include the following: total trabecular and cortical mineral content; cortical cross-sectional area and thickness; and biomechanical strength indices calculated from density and area (ie, bone strength indices, polar section modulus, and polar strength strain index) [86]. Outcomes are calculated using a validated open source image analysis software package (Fiji distribution of ImageJ) [87,88].

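### All outcomes are tested at P≤.05 with no stated control across outcomes and no named primary variable, so the chance of a false beneficial change somewhere is well above 5%

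*Protocol article*

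**What the plan says.** Under Quantitative and Qualitative Analyses, the rule is: "Whenever applicable, the level of significance will be set at" P≤.05, and it covers every test. For Hypothesis 1, each outcome gets a repeated-measures ANOVA or a Friedman test, "with planned comparisons based on the hypothesis and Bonferroni correction will be conducted to detect significant time effects", with particular interest in three contrasts: "for the preintervention (T_0_ vs T_1_), intervention (T_1_ vs T_2_), and retention (T_2_ vs T_3_) phases". No correction, ordering or hierarchy across outcomes is given.

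Under Sample Size Estimation, the calculation rests on change "in both body composition and bone mineral density (ie, main outcomes"). That label covers two families. The sentences that follow size the study on one variable from each, leg lean mass by DXA and tibial density by pQCT, but call neither one primary.

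The families are wide. Under Bone Mineral Density and Architecture, "reported pQCT outcomes will minimally include the following": a list of about seven parameters, at three imaging sites. The question behind Hypothesis 1 (Objectives) is whether the program will "induce beneficial changes on musculoskeletal, cardiorespiratory, and endocrine-metabolic health; wheelchair-related functional skills and mobility; and psychosocial outcomes". The Outcomes overview says that "All outcomes reflecting the potential impacts of the intervention based on the logic model" are collected at all four visits, apart from the satisfaction measures.

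**The concern.** Bonferroni within an outcome limits error over visits for that outcome. It does nothing about the number of outcomes. If any variable in any domain can be read as support for Hypothesis 1, the relevant error rate is the chance that at least one of them shows a favourable change when the program does nothing. The 5% level used in the sample size calculation does not describe that rate.

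The consequence is sharper here because the study is self-controlled, with no concurrent group against which to check a chance finding. The Discussion expects the results to inform purchasing, referral and public funding decisions. A claim resting on whichever variable crossed the threshold would be weak support for those.

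**Working it through.** **The plan's own figure.** The article states no familywise error rate; its figure is n = 18 for 80% power at 5%. The inputs are lean mass 14.0 to 15.8, SD 2 (d = 1.8/2 = 0.90) and density 466 to 532, SD 70 (d = 66/70 = 0.943). With the two-sample normal formula, n per group = 2(1.960 + 0.842)²/d², which gives 19.4 for lean mass and 17.7 for density, so 20 and 18. A paired t calculation with those SDs as SDs of change needs about 12 and 11. The stated 18 is therefore close to a two-sample n per group, which leaves the meaning of the SDs uncertain. This matters for the power figures below.

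**Counting outcomes.** A minimum reading of the Outcomes section gives: vital signs 3, pain 4, range of motion 3, strength 3, spasticity 1, propulsion tests 4, wheelchair skills scores 3, DXA density 3, pQCT bone 7 × 3 = 21, body composition 8 (fat and lean; total and three regions), muscle 6, blood 17, gas analysis 1, quality of life 6, psychological scales 3. The total is 86. I use 60 to 88 as the range.

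**Counting main outcomes.** Body composition 8, DXA density sites 3, and 1 to 3 density or mineral-content variables at each of 3 pQCT sites give 8 + 3 + 3 = 14 to 8 + 3 + 9 = 20. Counting all seven pQCT parameters gives 8 + 3 + 21 = 32, but that includes area, thickness and strength measures, which are not density.

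**Error per outcome.** I assume two-sided tests and three planned contrasts. Then T1 vs T2 is tested at .05/3 = .0167, or .05/6 = .0083 in the beneficial direction.

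**Chance of at least one false T1-T2 result, independent outcomes.** The formulas are 1 − (1 − .05/6)^m for beneficial and 1 − (1 − .05/3)^m for either direction.

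| m | Beneficial | Either direction |
|---|---|---|
| 14 | 11.1% | 21.0% |
| 20 | 15.4% | 28.5% |
| 32 | 23.5% | 41.6% |
| 60 | 39.5% | 63.5% |
| 88 | 52.1% | 77.2% |

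The beneficial figure passes 50% only at about 83 independent outcomes.

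**With correlation** (equicorrelated normal test statistics):

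| Pairwise correlation | Beneficial, m = 60 | Beneficial, m = 88 | Either, m = 60 | Either, m = 88 |
|---|---|---|---|---|
| 0.1 | 34% | 43% | 61% | 74% |
| 0.3 | 24% | 30% | 48% | 58% |
| 0.5 | 17% | 20% | 33% | 39% |

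**Any false overall time effect** at .05, independent: 1 − .95^60 = 95% and 1 − .95^88 = 99%.

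**With two named primaries at .025 each**, independent: 1 − .975² = 4.9%.

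**Power of that alternative** (paired t, n = 18, two-sided .025):

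- Stated SDs are SDs of change: 90% (d = 0.90) and 93% (d = 0.943).
- Stated SDs are between-person, pre-post correlation 0.3: the SD of change is the stated SD × √(2 × 0.7) = 1.183 × SD, so d = 0.761 and 0.797, and power is about 77% and 81%.
- Stated SDs are between-person, correlation 0.5: the factor is 1, so power is again 90% and 93%.

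**The case against.** The strongest reply has four parts.

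1. **Direction and dependence.** Hypothesis 1 concerns benefit, so the 64% to 77% range for either direction includes apparent harm. Independence is also unrealistic: regional masses add up to totals, and the pQCT strength indices are calculated from density and area. This stands. A reader might infer that a false beneficial finding is more likely than not unless outcomes are strongly correlated. The figures do not support that: 50% is passed only near the top of the count with almost no correlation.
2. **Other criteria.** Hypothesis 1 asks that effects be meaningful as well as significant and exceed control-phase change, and the Study Design section adds patient-specific minimal detectable change criteria. An isolated P value is thus not the whole test. If the contrasts were also run only after a significant overall test (not stated), a simulation with n = 20 and independent outcomes puts the beneficial rate at 27% for 60 outcomes and 36% for 90. This lowers the figures but leaves them far above 5%, and the article does not say how these criteria combine with the P values.
3. **The Bonferroni family is not defined.** Confining it to visits is an inference, though the natural one, since the correction is attached to comparisons that detect time effects.
4. **A separate analysis plan might set a hierarchy.** It might, but the article does not merely leave the matter open: it fixes P≤.05 for all tests. Any hierarchy would have to depart from that sentence.

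**Conclusion.** The concern holds in a moderate form. As written, the plan gives a chance of at least one false beneficial T1-T2 change of about 40% to 52% across 60 to 88 independent outcomes, 24% to 30% at correlation 0.3, and 17% to 20% at 0.5. Within the main-outcome families, counted as 14 to 20 density and body composition variables, it is about 11% to 15% in the beneficial direction if independent. A reader might put this at 23% (42% in either direction) by counting 32 variables, but the article's label is bone mineral density, so architecture and strength measures do not clearly belong.

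The results assume two-sided tests, three planned contrasts per outcome and no true effect on any outcome. The independent-case figures are upper-end values for the reasons above. The conclusion does not depend on crossing 50%: even at correlation 0.5, the rate across all outcomes is more than three times 5%. This should be corrected. It affects what the study may claim as confirmed, not whether it can be run.

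**What to change.** In the Statistics section, name leg lean mass by DXA and tibial bone mineral density by pQCT as the two primary outcomes. Test each on T1 vs T2 at .025, or use Holm across the two. State that all other outcomes are exploratory and reported with estimates and confidence intervals, and that their P values do not confirm Hypothesis 1. Say also whether the stated SDs of 2 and 70 are SDs of change.

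The cost is a change of wording and fewer outcomes that can be claimed as demonstrated. No participants or measurements are added. One might infer that the stated 80% power is kept in every case. That is so if the SDs are SDs of change, but with between-person SDs and a pre-post correlation of 0.3, lean mass falls slightly below 80% at n = 18.
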